## Abstract

**Background:**

Sexually active women aged 18 to 48 are within the population at risk for acquiring sexually transmitted infections. Some STIs can cause serious complications in women’s reproductive health. Accordingly, this practical randomized trial aims to evaluate the effect of an interventional education based on the ISD model on improving preventive behaviors for Iranian women.

**Methods:**

Women aged 18–48 years that refer to Tehran Municipality Health Houses will be invited to join the study. Recruitment will continue until a sample of 150 women participants. The study will be conducted using a mixed-methods protocol in three phases. In the first phase, women’s educational and learning needs about STIs will be identified using a qualitative approach. In the second phase, the results from the qualitative approach will be used to design a training program based on an ISD model. The educational intervention will be performed in the third phase. Participants will be randomly allocated into two groups: (1) the intervention group and (2) the control group. Data will be collected using STI Four-Scale of Preventive Behaviors at baseline, immediately, 1-month, and 3-month follow-up assessments. The impact of the intervention on the promotion of preventive behaviors from STIs will then be evaluated.

**Discussion:**

This study provides an educational program for empowering and promoting behaviors that prevent STIs. If the designed interventions in the present study are effective, it has practical potential to be generalized for Iranian women at risk of STIs.

**Trial registration:**

ClinicalTrials.gov IRCT20200602047638N1. Registered on 22 May 2021 with the IRCTID, V1.0.

## Background

In both developed and developing countries, sexually transmitted infections (STIs) are regarded as one of the most serious public health issues [1] More than a million people are infected with STIs every day around the world, and 50 million are infected with one of four curable sexually transmitted bacterial infections, namely chlamydia, gonorrhea, syphilis, and trichomoniasis [2]. The World Health Organization (WHO) estimated in 2008 that the total incidence of four preventable STIs in the Eastern Mediterranean region was 26.4 million [3]. Although the risk of HIV infection and death has decreased in most areas of the Middle East and North Africa, the virus’s prevalence is increasing. The actual prevalence of STIs in Iran is much higher than official data and records indicate [1, 4].

The Ministry of Health and Medical Education in Iran presented alarming statistics on the rate of STIs (such as AIDS) and their rate of transmission through sexual contact. According to reports, sexual transmission has increased from 10 to 21%, and 38.9% of the 28,000 cases registered in 2013 acquired it through unsafe sex [5]. Furthermore, 1700 cases of gonorrhea and 5500 cases of chlamydia have been reported in Iranian men and women. These infections were found to be slightly more common in women than in men [6].

Some STIs can cause serious complications, including pelvic inflammatory disease, infertility, ectopic pregnancy, cervical cancer, neonatal death, or congenital anomalies. Meanwhile, these infections can facilitate the spread of bloodborne diseases such as the human immunodeficiency virus (HIV) and hepatitis B virus via sexual contact [7]. In addition to the sexual route, blood product transfusion, mother-to-child breastfeeding, intrauterine, and delivery are all known ways for some STIs to be acquired [8]. STI complications have a disproportionate impact on people of all ages, with significant consequences for women of reproductive age. Women are biologically more vulnerable to such STIs than men, and they are more likely to experience problems as a result [9]. Women who engage in sexual activity are at risk for STIs [10, 11].

Current efforts to prevent the spread of STIs are insufficient and despite significant efforts to identify simple interventions for reducing high-risk behaviors, changing behavior remains a complex challenge [3]. Several reasons highlight challenges in sexual health education in particular STIs. The results of a review study show that, in general, Muslim women have poor knowledge about the signs and symptoms of STIs, how to prevent, diagnose, and treat them, in addition to many concerns. wrong concept. Negative attitudes towards people living with HIV/AIDS are widespread, and this attitude is strongly influenced by misconceptions and inadequate knowledge. Infected women tend to face more blame and judgment than men [12]. The fact that the mere existence of sexually transmitted infections (STIs) in Iran and other Muslim countries is considered taboo by the government and the public has created a state of denial, which is what some call “a health crisis behind the veil.” [13–15]. Furthermore, individuals’ access to effective resources has been hampered in many developing countries due to negative attitudes toward sexual health education, ineffective communication skills, insufficient educational materials, and a lack of knowledge [16].

Despite being prohibited in the religion of Islam, premarital and extramarital sexual relationships are by no means non-existent, and the scarce literature dedicated to sexual practice in Iran confirms this [16]. Moreover, the incidence of premarital sex has increased over the years [17, 18]. Iranians’ sexual health may be jeopardized as a result of receiving incorrect sexual information from the internet and other sources [19, 20]. Furthermore, discussing STIs is a cultural constraint and taboo [21].

From 2010 to 2013, the third national program on AIDS and STIs in Iran included four STI strategies such as education, sexual transmission prevention, treatment, and strengthening of the epidemiological care system with data management [22]. Educational intervention is one of the most effective strategies for behavior change [23]. The educational approach’s goal is to provide people with the knowledge, information, and skills they need to adopt healthy behaviors. Also, behavioral approaches use preventive strategies to encourage individuals to adhere healthy behaviors [24]. Globally, the prevention of high-risk behavior and unprotected sex, as well as the promotion of healthy behavior, has been identified as the most effective solutions for STI prevention [25]. The timely and rapid diagnosis of disease, complete and effective treatment, education on prevention and risk reduction, and encouraging the use of condoms are some of the principles that can control and cure STIs [26].

In general, health-related behavior and its determinants are defined as “personal attributes such as beliefs, expectations, motivations, values, perceptions, and other cognitive factors.”; personality traits, including affective and emotional states and characteristics; and manifest behaviors, actions and habits related to the maintenance of health, the restoration of health and the promotion of health” [23]. A growing body of literature specifies that behavioral interventions with clear conceptual frameworks or theories are more effective than those without [27]. Measuring the use of behavioral theories/models is a key step in supporting theory/model-based behavioral interventions [28, 29]. In line with this, several studies have shown that theory-based training programs are effective in improving sexually transmitted disease prevention behaviors in Iranian women [30–32]. Given the above, it seems that educational interventions based on theories that consider the learning needs of the target group will be effective in promoting preventive behaviors of sexually transmitted infections in at-risk women. Therefore, this study mixes methods will be used to design and evaluate an educational program to promote preventive behaviors of STIs among at-risk Iranian women.

### Hypothesis

The main aim is to assess the impact of an educational program based on the ISD model on improving preventive behaviors for STIs Iranian women. Intervention effects will be examined at 4 months. The research hypotheses are as follows:The intervention group will show higher preventive behaviors for STIs than the control group measured by mean scores.The intervention group will show STI knowledge more than the control group measured by mean scores.The intervention group will show STI vulnerability than the control group measured by mean scores.The intervention group will show STI prevention self-efficacy more than the control group measured by mean scores.The intervention group will show STI prevention intentions more than the control group measured by mean scores.

### Trial design

The evaluation design is a parallel, randomized controlled trial, with two arms and with a 1:1 allocation ratio. The intervention arm will receive the training program starting in June 2022, and the control arm will receive the training program after the final research data collection, with training from June 2023. If the trial is not able to recruit 63 women within the recruitment period, then the research team will consider an unequal allocation ratio with a smaller number of participants in the control group or extending data gathering time. The impact of this is discussed in the section on sample size.

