### Sample size and power calculations

The sample size we require in the quantitative phase to provide sufficient power was calculated as 63 persons for each group. This sample size was calculated to be adequate at an alpha of 0.05 and a power of .80, to test for a difference between the groups. we considered a potential dropout rate of 30%. According to the formula below, we should start with a recruitment target of 75 participants in each group:

In accordance with this approach, a total of 150 women at risk, aged 18 to 48, from the Tehran Municipality Health House, will be recruited using the inclusion and exclusion criteria listed in Table 1.

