### Randomization and blinding

After informed consent and baseline data collection, participants in the randomized controlled trial will be randomly assigned to the intervention and control arms in a restricted randomized block design. A research identification number will be given to each woman. Then, the identified individuals who volunteered to participate in the study were randomly assigned to the experimental and control groups using a blocking method. Following simple randomization procedures, participants will be assigned to one of two trial arms in a 1:1 ratio based on a computerized randomization program via https://www.sealedenvelope.com/simple-randomiser/v1. The letter A will be considered for the intervention group1 and the letter B for the control group. The process of random allocation will be continued continuously until the sample size will be reached. Masking of participants and study staff is not possible due to the nature of the intervention (educational) and allocation ratio. The first researcher ([name]) will enroll participants in the study and allocate them a unique ID number. A statistic expert out of the research team ([name]) will generate the allocation sequence using the women’s numbers. The first researcher ([name]) will then inform women which group they have been allocated to.

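### The low-recruitment rule is triggered by the wrong number, and one of its two options, a smaller control group, would cost power for the same total

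*Protocol article*

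**What the plan says.** The Trial design section sets a parallel trial "with two arms and with a 1:1 allocation ratio". It then adds a contingency: "If the trial is not able to recruit 63 women within the recruitment period", "the research team will consider an unequal allocation ratio with a smaller number of participants in the control group or extending data gathering time". It gives no ratio, no lower limit for the control group and no order of preference between the two options. It closes with "The impact of this is discussed in the section on sample size".

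Sample size and power calculations says the required number "was calculated as 63 persons for each group", which is described as "adequate at an alpha of 0.05 and a power of .80, to test for a difference between the groups". That section then allows for 30% dropout and sets a recruitment target of 75 per group. The total of 150 appears there and under Participants. The visible text of the section does not mention unequal allocation.

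Two other sections bear on the rule. Randomization and blinding says "participants will be assigned to one of two trial arms in a 1:1 ratio based on a computerized randomization program", with no exception, and describes allocation as running on until the sample size is reached. The intervention programs section describes open-ended recruitment up to the required size, with all participants allocated at that point.

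**The concern.** A shortfall rule is a decision threshold, so its number and its action should both serve the design. Here neither does.

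The number is the per-group analysis requirement, not a recruitment target, so a trial well short of target need not trigger the rule. The action in the first option moves women between arms without adding any. When the total is already low, that reduces precision further. Someone applying the rule would also find no limit on how far the ratio may go, no support for it in the randomisation section, and no account of its effect where the article says one is given.

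**Working it through.** **Inputs.** From the sample-size section: 63 per group, alpha 0.05, power 0.80, dropout 30%, recruitment target 75 per group (150 in total). From the Trial design section: a trigger of 63 women. Assumed: a two-sided test, equal SDs and a standardised difference d. No effect size or SD is visible because the formula did not survive text extraction, so d is back-solved and a range is shown. The ratios and the total of 100 are illustrations; the plan specifies neither.

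**Reproducing 63.** n per group = 2(z₀.₉₇₅ + z₀.₈₀)²/d² = 2(1.960 + 0.842)²/d². With d = 0.5 this is 62.8, rounded up to 63. Solving back from 63 gives d = 0.499. A one-sided test at d = 0.5 would need only 50. The figure of 63 therefore fits d = 0.5, two-sided, but this is an inference.

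**Trigger.**
- Literal reading, 63 in total: the rule acts only below 63, so it is silent from 63 to 149. Power at 63 in total, split equally, is about 50–51% before any dropout.
- Charitable reading, 63 per group (126 in total): the rule is silent from 126 to 149. If 63 per group were recruited and 30% lost, 63 × 0.7 = 44 per group would remain. Power is then Φ(0.5 × √(44.1/2) − 1.96) = Φ(0.39), about 65%.

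On neither reading does 63 match the target of 75 per group.

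**Smaller control group.** For intervention:control = k:1 and total N, the variance of the mean difference relative to 1:1 is (1/n₁ + 1/n₂)/(4/N) = (1 + k)²/(4k). This is 1.042 at 1.5:1, 1.125 at 2:1 and 1.333 at 3:1. It is smallest at k = 1 whatever the effect size.

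Power at d = 0.5, two-sided 0.05 (normal approximation / t-test):

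| Ratio | Total 126 | Total 100 | Total needed for 80% (normal) |
|---|---|---|---|
| 1:1 | 80.1% / 79.5% | 70.5% / 69.7% | 126 |
| 1.5:1 | 78.5% / 77.9% | 68.8% / 67.9% | 133 |
| 2:1 | 75.4% / 74.7% | 65.4% / 64.6% | 144 |
| 3:1 | 68.1% / 67.4% | 58.1% / 57.3% | 168 |

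Example: at N = 100 and 2:1, Φ(0.5/√(1/33.3 + 1/66.7) − 1.96) = Φ(0.397) = 65.4%.

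**Range of d.** At a total of 100, going from 1:1 to 2:1 changes power from 51.6% to 47.0% (d = 0.4), 85.1% to 80.7% (d = 0.6) and 97.9% to 96.5% (d = 0.8). The direction is the same throughout.

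**Passages set side by side.** Trial design allows an unequal ratio; Randomization and blinding does not mention one. Trial design sends the reader to the sample-size section for the impact; that section's text has nothing on it. The missing formula is introduced as giving the 75-per-group target, so it is unlikely to be the promised discussion.

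**The case against.** The rule is mild. The team will only consider a smaller control group, and more time is offered as an alternative. The contingency is stated in the same paragraph as the 1:1 ratio, so it is an announced exception. The loss is under 2 points at 1.5:1, and 63 women is probably loose wording for 63 per group. All of this is fair. It means that the planned 1:1 comparison is unaffected unless the option is used, and that the 50% power figure belongs to the less natural reading. It does not repair the trigger, which misses the recruitment target even when read per group, and nothing in the plan confines the imbalance to a mild one.

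A reader might also infer that changing the ratio would confound arm with enrolment date. The documents do not establish this. If the ratio changed during the continuous allocation described under Randomization and blinding, arm would be tied to enrolment date. If all women are allocated once recruitment is complete, as The intervention programs section says, one ratio could apply to everyone and the problem does not arise. The article supports both pictures, so the risk is conditional.

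**Conclusion.** The point holds as a defect in a contingency rule. The trigger does not match the recruitment target of 75 per group and 150 in total. The unequal-allocation option can only lower power for a given total if SDs are equal. The randomisation section does not provide for that option, and the cross-reference leads to no discussion of it.

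At a total of 100 the loss against 1:1 is 1.8 points at 1.5:1, 5.1 at 2:1 and 12.4 at 3:1. These sizes rest on d = 0.5, two-sided testing and ratios the plan never states; the direction does not depend on d. It would go too far to say that the plan commits to shrinking the control group, or that its main comparison is biased: the text supports neither.

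**What to change.** - Delete the unequal-allocation option and state that allocation stays 1:1 throughout.
- Meet a shortfall by extending the recruitment or data-gathering period, saying which is meant; the present sentence mentions only data gathering. If recruitment still stops early, state the power at the achieved 1:1 size.
- Restate the trigger against the actual recruitment target, now 75 per group and 150 in total. First resolve a separate inconsistency: with 30% dropout, 75 × 0.7 = 52.5, so 75 recruited does not leave 63 analysable per group. Pairing 150 randomised with 63 analysable per group in the revised sentence would carry that error over.
- Remove the cross-reference to the sample-size section.

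The cost is a change of wording and possibly a longer recruitment period.

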## Methods

### Aim, design, and outcomes

This practical randomized trial aims to evaluate the impact of an educational program based on the ISD model on improving preventive behaviors of STI Iranian women. An exploratory sequential mixed-methods design will be used in the study.

### Outcome measures

The initial research questions addressed in this study are “Does the educational intervention based on Instructional System Design (ISD) model affect STI preventive behaviors among Iranian women?”. To answer this main question following primary outcomes are expected:Determining and comparing the effects of an educational intervention designed based on the ISD model in STI knowledge among women in the target and control groups before, immediately one month, and three months after the interventions.Determining and comparing the effects of an educational intervention designed based on the ISD model in STI vulnerability among women in the target and control groups before, immediately, one month, and three months after the interventions.Determining and comparing the effects of an educational intervention designed based on the ISD model in STI prevention self-efficacy among women in the target and control groups before, immediately, one month, and three months after the interventions.Determining and comparing the effects of an educational intervention designed based on the ISD model in STI prevention intentions among the target and control groups before, immediately, 1 month, and 3 months after the interventions.

Consequently, we expect the effect of our educational intervention on preventive action regarding STIs among women. To assess the expected secondary outcomes a self-reported assessment addressing preventive actions (using a condom, doing pap-test and genital examination) will be conducted.

### Ethical approval

This protocol and the template informed consent forms will be reviewed and approved by the sponsor and Medical Ethics Research Center of Tarbiat Modares University (reference: IR.MODARES.REC.1399.039). with respect to scientific content and compliance with applicable research and human subjects regulations. The protocol, site-specific informed consent forms (Persian language), participant education and recruitment materials, and other requested documents—and any subsequent modifications—also will be reviewed and approved by the ethical review bodies. Subsequent to the initial review and approval, Ethical Committees (TMU) will review the protocol at least annually. The Investigator will make safety and progress reports to the TMU at least annually and within six months of study termination. These reports will include the total number of participants enrolled . . . and summaries of each stage of intervention [33].

### Consent or assent

A trained research health educator will introduce the trial to participants who will receive a pdf file regarding the main aspects of the trial. participants will also receive information sheets. Trained Research will discuss the trial with participants in light of the information provided in the pdf file and information sheets. participants will then be able to have an informed discussion with the participating consultant. Trained Research will obtain written consent from participants willing to participate in the trial. Information sheets and consent forms are provided for all involved in the trial however these have been amended accordingly in order to provide separate information sheets and consent form. All information sheets, consent forms, and the pdf file are in the Persian language There are also separate information sheets and consent forms for the control group.

### Participants

The research population will include women aged 18–48 years who are sexually active. To meet these inclusion criteria, recruitment will be from women who refer to Tehran Municipality Health House Participants will be recruited from Tehran Municipality Health House affiliated by the Women Empowerment Headquarters of Tehran Municipality. The list of introduced eligible participants will be initially contacted via phone and given an in-depth description of the study, those interested will be followed up with an inclusion listing. Once Tehran Municipality Health House has received a briefing about the project and understands the randomized controlled trial design and data collection elements of the study, it will be asked to sign the consent form and allocate one room for the research project. Invitations to participate in the study will be stretched to all eligible women until we reach a sample size of 150 women who provide informed consent to participate. Table 1 contains a complete list of the inclusion and exclusion criteria.

**Table 1 Tab1:** Inclusion and exclusion criteria

Inclusion criteria	Exclusion criteria
• Women aged 18–48 years • Women without cervical cancer • Women without mental disorders, drug dependence, and addiction • Tend to participate with informed consent to share information, and participate	• Absence of more than two sessions in training sessions • The participant has a special illness that is not able to participate in training sessions

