### Phase 3: the randomized controlled trial

Randomized controlled trials (RCTs) are the most effective way to assess public health interventions. RCT reduces the impact of confounding bias because each study participant is assigned to an intervention or control group solely by chance [38]. Figure 2 depicts the flow chart of the randomized controlled protocol.

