### Strategies to improve adherence to interventions

Women are required to be present at the study site in person to receive the intervention, and any missed sessions are recorded to check adherence. To improve adherence, training program times are flexible between 9am and 5pm each day (room availability permitting), are not required to be at the same time of day, and are not required on weekends. Participants will be arranged for a free visit with a trained midwife for genital examination and health counseling.

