### Methods for additional analyses (non-adherence and missing data)

Missing data will be reported and links between results reviewed. depending on the extent of data missing an appropriate sensitivity analysis will be performed.

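### Table 1 makes missed training sessions an exclusion criterion, a rule that during the compared period can remove only randomised women in the intervention arm

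*Protocol article*

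**What the plan says.** Five statements in the protocol article bear on this point.

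- **Participants, Table 1.** One of the two exclusion criteria is "Absence of more than two sessions in training sessions". The text introducing the table says "Table 1 contains a complete list of the inclusion and exclusion criteria".
- **Randomization and blinding.** "After informed consent and baseline data collection, participants in the randomized controlled trial will be randomly assigned", so allocation comes before any training.
- **Trial design.** The trial is parallel, "with two arms and with a 1:1 allocation ratio", and "the control arm will receive the training program after the final research data collection".
- **Strategies to improve adherence to interventions.** Attendance appears here as an adherence measure: "any missed sessions are recorded to check adherence".
- **Methods for additional analyses (non-adherence and missing data).** Non-adherence is named in the heading, but the text deals only with missing data: "depending on the extent of data missing an appropriate sensitivity analysis will be performed".

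Phase 3 justifies the randomised design on the ground that "each study participant is assigned to an intervention or control group solely by chance".

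**The concern.** An exclusion criterion should be decidable before allocation, or at least apply to both arms alike. This one does neither. Attendance cannot be observed at enrolment, and controls have no session to miss until the trial's data are complete. Followed as written, the rule compares intervention women who kept attending with a control group that has had no such selection.

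The outcomes are self-reported scores for STI knowledge, vulnerability, self-efficacy and intentions, plus self-reported preventive actions. If women who keep attending would have scored differently from those who stop, even without training, that difference enters the estimated effect. The protection by chance that Phase 3 relies on is then lost for the women analysed. If excluded women are also not followed up, no later analysis can recover their data.

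**Working it through.** **Step 1: timing.** This is a check of sequence and needs no figures.

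| Event | Intervention arm | Control arm | Section |
|---|---|---|---|
| Consent, baseline | before allocation | before allocation | Randomization and blinding |
| Allocation | before any session | before any session | Randomization and blinding |
| Training sessions | before the post-intervention assessments | none | Trial design |
| Last assessment | 3 months after the intervention | same | Outcome measures |
| Control training | – | after the last assessment | Trial design |

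Absence from more than two sessions can therefore be observed only after allocation and, within the compared period, only in the intervention arm.

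**Step 2: size, as an illustration.** The article states no figure to reproduce. It does not give the number of sessions, the expected share of women who would miss more than two, or how attendance relates to the scores. Those are assumptions below. The one document input is 75 women per group (Sample size and power calculations). The 30% row equals the dropout allowance in the same section and is an upper scenario, because it attributes the whole allowance to this rule. The setting is no true effect, a single unadjusted post-intervention comparison, outcome SD of 1, and 75(1 − q) against 75 women, where q is the share of the intervention arm excluded.

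*Model A: fixed gap.* Let attenders and non-attenders differ by g SD. The full arm has mean 0 = (1 − q)·m_att + q·m_non, with m_att − m_non = g. Hence m_att = q·g, which is the bias. The standard error is √(1/[75(1 − q)] + 1/75): 0.173 at q = 20% and 0.180 at q = 30%. Type I error is the rejection probability of a two-sided 5% t-test at that shift.

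| q | g (SD) | Bias = q·g (SD) | Women | Type I error |
|---|---|---|---|---|
| any | 0 | 0 | – | 5% |
| 20% | 0.5 | 0.10 | 60 vs 75 | 8.8% |
| 30% | 0.5 | 0.15 | 52.5 vs 75 | 13.1% |
| 20% | 0.8 | 0.16 | 60 vs 75 | 15.1% |
| 30% | 0.8 | 0.24 | 52.5 vs 75 | 26.3% |

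*Model B: correlated attendance and outcome.* Attendance propensity and outcome are bivariate normal with correlation ρ, and the lowest fraction q is removed. Bias = ρ·φ(z_q)/(1 − q). For example, at q = 30% and ρ = 0.5, z_q = −0.524 and φ = 0.348, so bias = 0.5 × 0.348/0.7 = 0.248 SD. Type I error uses the normal approximation with the reduced variance of the truncated arm.

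| q | Bias (SD), ρ = 0.1 / 0.3 / 0.5 | Type I error, ρ = 0.1 / 0.3 / 0.5 |
|---|---|---|
| 10% | 0.019 / 0.058 / 0.097 | 5.2% / 6.4% / 9.1% |
| 20% | 0.035 / 0.105 / 0.175 | 5.5% / 9.4% / 18% |
| 30% | 0.050 / 0.149 / 0.248 | 5.9% / 13.4% / 30% |

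With ρ = 0 the bias is 0 and the error is 5%. If all randomised women are analysed as allocated, bias from this rule is 0 whatever q and ρ are.

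**Step 3: what the illustration leaves out.** Data analysis, Phase 3, plans a repeated-measures model that includes pre-intervention values, and also differences in means between the groups. The tables apply most directly to the latter. In a group-by-time contrast, any part of the gap already present at baseline would largely cancel, so the distortion would be smaller.

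**The case against.** **The row may mean something milder.** No sentence says that data from these women are discarded or that their questionnaires stop. The row could mean that training ends, or could mark women for a per-protocol set. The analysis population is commonly left to a statistical analysis plan that is not shown, and the flow chart is not shown either. This lowers certainty about the consequence, and the absence of a stated analysis set is not the complaint here. It does not rescue the wording. The row stands under exclusion criteria in a table described as complete, and nothing visible retains the women. An analysis plan that kept everyone would contradict Table 1, and the two would still need reconciling.

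**The direction is not established.** A reader might infer that the rule necessarily favours the intervention by keeping the motivated women. That is plausible, but the documents do not show it. Women may miss sessions because of work or cultural constraints, or because they already know the material. If attendance is unrelated to the outcomes, there is no bias.

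**The sizes are assumed.** This stands in full. The shares, gaps and correlations are not in the documents, the range starts at zero, and baseline values may absorb part of the effect.

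**Only the rule is one-sided.** A reader might also infer that the control arm stays complete. It need not: the sample size section allows for dropout without limiting it to one arm, and the Discussion expects losses at later assessments.

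**The illness criterion.** A reader might extend the point to the other exclusion row, on illness that prevents attendance. That row reads naturally as a condition checked at enrolment, and nothing says it is applied later. It calls for a clarification and is not a second defect.

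**Conclusion.** The point holds as a defect in a stated rule. Table 1 excludes women on behaviour that can be observed only after randomisation and, in the compared period, only in the intervention arm. It also conflicts with the article's own treatment of missed sessions as adherence. That much follows from the text without any assumption.

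The consequence is conditional: the comparison is biased if the rule is applied to follow-up or analysis and if attendance is related to the outcomes. The most plausible direction is towards the intervention, but this is not demonstrable. For an unadjusted comparison the illustrated bias runs from 0 to about 0.25 SD. The type I error runs from 5% to 26% (fixed gap) or 30% (correlated model) at the extreme of 30% excluded with a strong relation. These are upper scenarios and not estimates for this trial. The correction is still needed before follow-up proceeds, because it protects the randomised comparison itself and data that were never collected cannot be restored.

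**What to change.** - Delete the absence row from the exclusion criteria in Table 1.
- State that follow-up questionnaires go to every randomised woman, whatever her attendance.
- State that the primary analysis includes all randomised women in their allocated arm.
- Report absence from more than two sessions as non-adherence, using the attendance records already planned. Present any attendance-restricted analysis only as a labelled sensitivity analysis.
- As a clarification only, say that the illness criterion is assessed before randomisation.

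The cost is a change to Table 1, a few sentences on follow-up and analysis, and the effort of following up women who stopped attending. The estimated effect may be somewhat smaller, since women who received little training stay in the intervention arm. No figure stated in the article has to change for this point.
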